#### **11.4 Trial closure**

The treatment phase will be followed by a non-interventional follow up period which will continue for 8 weeks after the last participant completes protocol treatment.

For the purposes of the Research Ethics Committee approval, the study end date is deemed to be the date of last data capture. The expected end date is 01/02/2012.

## 12.0 Statistical considerations

### 12.1 Randomisation

Randomisation will take place centrally after confirmation of eligibility by a telephone call to the WCTU. Participants will be randomised using balanced blocks. This will ensure balanced treatment allocation by a number of clinically important stratification factors. Randomisation will have an allocation ratio of 2:1.

### 12.2 Outcome measures

#### 12.2.1 Primary outcome measure

*Adherence to NMES:* Proportion of patients completing a pre-determined level of compliance to the recommended NMES programme (NMES for 30min three times a week) measured using a self-report daily diary.

To comply, participants must complete three sessions during each week of chemotherapy, sessions of use must be for the full 30 minutes for each individual day, use beyond 30 minutes in one session or beyond the three required sessions per week can not be carried over and missing diary data will be treated as non-compliance

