### 6.1 Inclusion criteria

Patients meeting all of the following criteria may be included in the trial:

- Aged 16 years or older
- ECOG Performance Status score of 0, 1 or 2
- Is scheduled to receive 3–4 cycles of first line palliative chemotherapy
- Able to use NMES device
- Life expectancy > 3 months
- Has provided written informed consent.

The researcher must confirm the eligibility of a patient in the patient's medical notes prior to randomisation.

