#### NMES programme

NMES for 30min daily at home to the anterior thighs throughout chemotherapy. Because patients are generally anxious about starting chemotherapy we will defer initiating NMES until one week after commencing cycle one.

A physiotherapist will supervise the first session of NMES either at hospital or in the patient's home depending on patient preference. This will be supplemented by written instructions, weekly phone calls and home visits if required. When conducting home visits the physiotherapist will follow the WCTU home safety procedure SOP and a buddy system SOP.

Stimulation will be delivered using a MicroStim Exercise Stimulator MS2v2 (Odstock Medical Ltd, Wiltshire, UK) and self-adhesive electrodes placed over the body of the quadriceps. This is a CE marked (CE 02104) Class IIa Medical Device and the application is in accordance with the CE marking reference for the device.

The proportion of the treatment duration which is active, i.e. the stimulation phase of the duty cycle, will increase on a weekly basis from 11% to 18% to 25%, remaining constant thereafter.

The intensity or amplitude (device output 0–120mA, tested across 1000 $\Omega$ ) will initially be set to elicit a visible and comfortable muscle contraction.

Thereafter, patients will be encouraged to increase the amplitude as tolerated during the monitoring phone calls.

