| NMES                  |                  |        |        |        |        |        |        |        |        |        |         |         |         |            |
| Daily application            |                  |        | X      | X      | X      | X      | X      | X      | X      | X      | X       | X       | X       |            |
| Supervision (home visit)     |                  |        | X      |        |        |        |        |        | X      |        |         |         |         |            |
| Supervision (telephone call) |                  |        |        | X      | X      | X      | X      | X      |        |        | X       | X       | X       |            |
| Adherence assessed           |                  |        |        |        |        |        |        |        |        | X      |         |         | X       |            |
| Interview (subgroup)         |                  |        |        |        |        |        |        |        |        | X      |         |         | X       |            |

*N.B. Serious Adverse Events (SAE) will be collected in real time via a designated SAE fax number.*

*Notes: the timing of assessments will be standardised to treatment cycles and thus will be sufficiently flexible to cope with delays during chemotherapy, e.g. due to neutropenia. The interview is completed either at week 9 or week 12 depending on the patient receiving 3 or 4 cycles of chemotherapy respectively.*

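### The primary adherence rule counts week 1 of chemotherapy, when no NMES is scheduled, and does not say whether the week 9 or the week 12 assessment decides

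*Protocol*

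**What the plan says.** Section 12.2.1 defines the primary outcome as the proportion of participants who reach a set level of compliance, and then fixes the rule in detail: "participants must complete three sessions during each week of chemotherapy". Each session must last the full 30 minutes. Use "beyond the three required sessions per week can not be carried over", and "missing diary data will be treated as non-compliance".

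The programme being measured is set out in Section 8.2. It is described as "NMES for 30min daily at home to the anterior thighs throughout chemotherapy", but its start is put back: "we will defer initiating NMES until one week after commencing cycle one". The schedule in Section 9.6 agrees. Chemotherapy is marked in weeks 1, 4, 7 and 10. The row labelled "Daily application" is blank in week 1 and marked from week 2 to week 12.

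The length of chemotherapy varies. Section 6.1 admits a patient who "Is scheduled to receive 3–4 cycles of first line palliative chemotherapy". End of treatment falls at week 9 (Section 9.3) or, for those who go on to a fourth cycle, at week 12 (Section 9.4). The schedule marks adherence as assessed at both weeks. Its footnote places the interview at week 9 or 12 "depending on the patient receiving 3 or 4 cycles of chemotherapy respectively", but gives no such rule for adherence. The same footnote ties assessment timing to treatment cycles so that delays can be absorbed.

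Section 12.3 applies one criterion to the result: at least 15 of 20 participants adhering, with 80% as the rate that supports a phase III trial and 50% or less as the rate that rejects one.

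**The concern.** The primary endpoint carries the trial's go/no-go decision, and its definition conflicts with the treatment schedule in the same document. Week 1 is a week of chemotherapy, so the rule asks for three sessions in it, and the programme provides none. The bar on carrying sessions over means that later use cannot make up for that week.

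Setting week 1 aside leaves a second gap. Every week must be passed, yet the number of weeks depends on how many cycles the participant receives, and no end point is named. Someone who passes every week to week 9 and misses a session in weeks 10 to 12 is a success at one assessment and a failure at the other. With 20 evaluable participants, each such case moves the proportion by 1/20, or 5 percentage points. If the window is chosen after the diaries have been seen, in an open trial, the choice is post hoc.

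**Working it through.** **1. The plan's own figure.** Inputs from Section 12.3: p0 = 0.50, p1 = 0.80, 90% power, p = 0.05. Sidedness is not stated; one-sided is assumed because it reproduces the stated number.

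n = [(1.6449 × √(0.5 × 0.5) + 1.2816 × √(0.8 × 0.2)) / (0.80 − 0.50)]² = [(0.8224 + 0.5126) / 0.30]² = 19.80, which rounds up to the stated 20.

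This depends only on the two proportions. Neither the defect nor the fix changes it.

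**2. The rule as written.**

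| Reading of a week of chemotherapy | Weeks counted | Week 1 included? | Sessions possible in week 1 |
|---|---|---|---|
| Every week of the course | 1–9 or 1–12 | Yes | 0 of 3 required |
| Only weeks in which a cycle is given | 1, 4, 7 and, for a fourth cycle, 10 | Yes | 0 of 3 required |

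Under either reading attainable compliance is 0%, and the probability of reaching 15 of 20 is 0.

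**3. Counting from the start of NMES** (scheduled timing, no chemotherapy delay).

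- Three cycles: weeks 2–9, 9 − 2 + 1 = 8 weeks, 8 × 3 = 24 sessions.
- Four cycles: weeks 2–12, 12 − 2 + 1 = 11 weeks, 11 × 3 = 33 sessions.

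The weekly requirement is the same for everyone. What differs is the number of weeks that must all be passed.

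**4. Direction.** To pass weeks 2–12 a participant must pass weeks 2–9 and three more, and nothing can be carried over. So for a given participant P(pass to week 12) ≤ P(pass to week 9). This needs no model.

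**5. Illustrative size.** The protocol gives no weekly adherence rate. Assume a constant weekly success probability q, independent between weeks and equal in both groups.

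- 80% over 8 weeks: q = 0.80^(1/8) = 0.9725, and q^11 = 0.736.
- 50% over 8 weeks: q = 0.50^(1/8) = 0.9170, and q^11 = 0.386.
- Anchored the other way, 80% over 11 weeks: q = 0.80^(1/11) = 0.9799, and q^8 = 0.850.

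At the opposite extreme, if each participant is either consistently adherent or consistently not, the two windows give the same proportion. At the 80% benchmark anchored on 8 weeks, the gap therefore runs from 0 (complete clustering) to 80.0 − 73.6 = 6.4 percentage points (independence).

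**6. Which assessment decides.** Section 9.6 marks adherence at weeks 9 and 12. Sections 12.2.1 and 12.3 name no time point. Section 12.5 gives time points for the secondary outcomes and for response, but none for the primary proportion.

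**The case against.** The strongest defence is that the compliance clause should not be read alone. Section 12.2.1 measures compliance with the recommended programme, Section 8.2 says when that programme begins, and the schedule leaves week 1 blank. Read together, the countable weeks are those with NMES. That is a sensible reading, and a result of 0 out of 20 is not a realistic forecast. But it corrects the stated rule rather than applying it. The point also cannot be left to the analysis plan, because the protocol itself fixes the rule and a plan that counted from week 2 would contradict it.

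The second defence is that adherence throughout each patient's own chemotherapy is a coherent thing to estimate. This stands. A varying course length is not an error in itself; the error is that the protocol does not say whether that is the window intended.

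A reader might infer that the 15-of-20 test is invalid because participants face different numbers of weeks. The documents do not support this. The 80% and 50% in Section 12.3 are proportions of all participants. If cycle number varies at random between participants, the number adhering is still binomial with that overall proportion.

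A reader might also infer a loss of power. If 80% is attached to three-cycle participants only, with independent weeks and equal weekly adherence, the chance of at least 15 of 20 falls from 0.804 (all three cycles) to 0.688 (half with four) and 0.559 (all with four). Section 12.3 attaches 80% to all participants, and on that footing the chance is 0.804 whatever the mix. Those who reach a fourth cycle may also adhere better. The fall is not a finding. (That 0.804 differs from the stated 90% power is a separate matter.)

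**Conclusion.** The primary compliance rule is wrong as written: it includes a week in which the programme schedules no NMES, so literal application gives 0% compliance. This rests on the text of Sections 8.2, 9.6 and 12.2.1 alone.

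The window is also undefined at its far end. It is 8 or 11 scheduled weeks, assessed at two times, with no statement of which feeds the decision. That the longer window is at least as hard for a given participant is certain. The size of the difference is not known from the protocol; 80% against 73.6% is an illustration under independence and equal weekly adherence, and clustering within participants would shrink it. The test and the sample size of 20 are unaffected. The rule needs correcting because it defines the primary endpoint and the correction is cheap.

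**What to change.** In Section 12.2.1, replace the reference to every chemotherapy week with: *each week in which NMES is scheduled, starting one week after the start of cycle 1*.

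Then name one deciding window for everyone, tied to cycles. The end of cycle 3 (scheduled weeks 2–9) fits best: the primary objective concerns patients having at least three cycles, and the drop-out allowance in Section 12.3 is counted to the same point. Report adherence during cycle 4 separately. A fixed run of 8 calendar weeks is not recommended, since Section 9.6 follows treatment cycles and a delay could close such a window before cycle 3 is finished. If the sponsor prefers each patient's full course as the primary window, say so and report the end-of-cycle-3 result as a sensitivity analysis. Carry the same wording into Sections 12.3 and 12.5.

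Cost: the weeks of cycle 4 no longer count towards the primary endpoint, and chemotherapy delays can still lengthen the window for some participants. The diary data are already collected and the NMES schedule stays as it is. Section 12.3 shows that recruitment of this open trial had begun, so this is a change to the primary endpoint and not just an edit. It should be made and documented before adherence data are reviewed, including at any interim analysis under Section 12.4.

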#### 12.2.2 Secondary outcome measures

*Safety of NMES:* toxicities will be assessed according to the NCI Common Terminology Criteria for Adverse Events (NCI CTCAE v3.0). Serious adverse events will be monitored in "real-time".

*Quadriceps muscle strength:* peak torque (kg) measured using a portable Manual Muscle Tester dynamometer (Lafayette Instruments, USA).

*Body composition:* lean tissue mass of the body and thighs (kg) assessed by low-dose dual energy x-ray absorptiometry (DEXA).

*Physical activity level:* mean daily step count assessed by a small, lightweight activPAL™ accelerometer worn on the thigh for one week.

*Response to chemotherapy:* overall objective clinical response categorised using Response Evaluation Criteria In Solid Tumours, documented from patients' medical reports.

*Nutritional intake:* mean daily energy (kJ/d) and protein (g/d) intake estimated from a 3-day food and drink diary.

*Fatigue:* Multidimensional Fatigue Inventory.

*Quality of life:* the EORTC-C30 and the lung cancer specific module LC-13.

*Experience of NMES:* semi-structured interview exploring patient experiences of completing NMES during chemotherapy.

### 12.3 Sample size calculation

This trial is powered as a Fleming's single stage phase II trial of the intervention arm. The main endpoint is the proportion of patients completing a pre-determined level of compliance to the recommended NMES programme (NMES for 30min three times a week) measured using a self-report daily diary. Following advice from the cachexia subgroup of the NCRI Palliative Care Clinical Studies Group we have determined that 80% of patients should adhere to this minimum level in order to warrant a future phase III study. Conversely, if  $\leq 50\%$  adhered to this minimum level, this would give grounds to reject further study. Using a Fleming's one stage method, 20 patients will be required to distinguish between these rates (90% power,  $p=0.05$ ) and if  $\geq 15$  out of 20 patients adhere, this would warrant further investigation.

We have included a randomised control arm into this trial design in order to allow comparison of some secondary end points. Originally the trial started by randomising with a 1:1 allocation; however this was changed to a 2:1 in favour of the NMES arm allocation part way through the trial in order to support recruitment. As the study analysis is based on a within-intervention arm analysis, the statistical integrity of the study is not affected. A local audit suggests about 25% of patients drop out before reaching 3 cycles. We

require 20 patients in the treatment arm to be available for analysis; therefore we estimate that 26 patients need to be recruited to this arm. At the time of the change in the randomisation allocation ratio this meant that 47 patients would need to be recruited in total (26 to the treatment arm and 21 to the control arm).

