## **12.5 Statistical analyses**

A full statistical analysis plan will be developed before the first interim analysis of the trial data.

For the primary endpoint, the proportion (and 90% confidence interval) of patients completing NMES for 30min three times a week will be reported.

For the secondary (intention to treat) analyses, change in leg muscle strength from baseline will be compared between trial arms at 9, 17 and 20 weeks.

Descriptive statistics will then be presented for the following measures at 9, 17 and 20 weeks:

- Change in QoL score from baseline
- Change in body composition from baseline
- Change in nutritional intake from baseline
- Change in fatigue from baseline

Response to chemotherapy at 9 and 12 weeks will be described in each trial arm.

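### The stated 90% power is a large-sample figure; the rule of at least 15 of 20 has exact power of 80.4% at 80% adherence

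*Protocol*

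**What the plan says.** Section 12.3 of the protocol gives the full specification of the primary design in a few sentences.

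- **Design:** "This trial is powered as a Fleming's single stage phase II trial of the intervention arm".
- **Target rate:** "we have determined that 80% of patients should adhere to this minimum level in order to warrant a future phase III study".
- **Unacceptable rate:** if 50% or fewer "adhered to this minimum level, this would give grounds to reject further study".
- **Size and power:** "Using a Fleming's one stage method, 20 patients will be required to distinguish between these rates (90% power", followed by p=0.05, with no statement of whether this is one- or two-sided.
- **Decision criterion:** at least 15 "out of 20 patients adhere, this would warrant further investigation".
- **Recruitment:** 26 patients enter the arm so that 20 can be analysed.

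Section 12.5 adds the form of the primary report: "For the primary endpoint, the proportion (and 90% confidence interval) of patients completing NMES for 30min three times a week will be reported". A 90% interval fits a one-sided 5% test. The protocol does not describe the 90% power as approximate and gives no other cut-off.

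**The concern.** Once the number of patients and an integer cut-off are fixed, power at a given true rate is a single binomial probability. Section 12.3 fixes both and prints 90% beside them, so the statement can be checked directly, and it is about ten percentage points too high.

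The figure describes the primary endpoint, and Section 3.0 gives the overall aim as helping to decide whether a phase III trial is feasible and justified. Anyone weighing a result just short of 15 would take it that a programme at the 80% target falls short only one time in ten. Under the rule as written it falls short about one time in five.

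**Working it through.** **Inputs, all from Section 12.3:** p0 = 0.50, p1 = 0.80, n = 20 analysable patients, cut-off 15, p = 0.05. I take 0.05 as one-sided, which matches the 90% interval in Section 12.5; the two-sided reading is checked in step 5. The 25% dropout does not enter, because the rule is tied to 20 analysable patients.

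**1. Reproduce the sample size.** The protocol cites Fleming's method without printing its formula. The usual one-sample normal approximation is

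n = [(z_α √(p0 q0) + z_β √(p1 q1)) / (p1 − p0)]²

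= [(1.645 × 0.5 + 1.282 × 0.4) / 0.3]² = 19.8, so 20. The stated size reproduces.

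**2. Reproduce the nominal power at n = 20.**

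Φ[(0.3 √20 − 1.645 × 0.5) / 0.4] = Φ(1.298) = 0.903. The stated 90% reproduces as a large-sample figure.

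**3. Reproduce the cut-off.** The large-sample critical value is 20 × 0.5 + 1.645 √(20 × 0.25) = 13.68. Fleming's rejection point is this value rounded to the nearest integer, plus one: 14 + 1 = 15. The stated cut-off reproduces.

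Steps 2 and 3 show where the gap arises. The 90.3% is the chance that a normal variable with mean 16 and variance 3.2 exceeds 13.68. The printed rule requires 15. With a continuity correction at 14.5, the same approximation gives 1 − Φ[(14.5 − 16)/√3.2] = 0.799.

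**4. Exact error rates of the printed rule.**

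- Power: P(X ≥ 15 | 20, 0.80), summing the terms for 15 to 20, is 0.1746 + 0.2182 + 0.2054 + 0.1369 + 0.0576 + 0.0115 = 0.8042. The chance of missing the criterion is 1 − 0.8042 = 0.1958.
- Type I error: P(X ≥ 15 | 20, 0.50) = (15504 + 4845 + 1140 + 190 + 20 + 1) / 2²⁰ = 21700 / 1048576 = 0.0207.

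Neighbouring cut-offs at n = 20:

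| Criterion | Exact one-sided α at 50% | Exact power at 80% |
|---|---|---|
| ≥14 of 20 | 0.0577 | 0.913 |
| ≥15 of 20 (protocol) | 0.0207 | 0.804 |
| ≥16 of 20 | 0.0059 | 0.630 |

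No row has both α ≤ 0.05 and power ≥ 0.90.

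**5. Sensitivity.**

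- *Sidedness.* The power of a fixed cut-off does not depend on it. Reading p = 0.05 as two-sided, the formula in step 1 gives 24.75, so 25 patients for 90% power, and nominal power at 20 patients is 81.7%.
- *True adherence.* Under the 15-of-20 rule, power reaches 90% only when true adherence is about 83.4%.

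**The case against.** The strongest defence is that the protocol follows the method it names. Fleming's large-sample procedure yields 20 patients, a cut-off of 15 and nominal power of about 90%, and Section 12.3 reports exactly these. That much stands. A reader might infer that the cut-off was mis-copied and that 14 was intended, since 14 is the first integer above 13.68 and 90% power belongs to it. The documents do not support that: the method's rejection point is 15, and at least 14 of 20 would exceed the protocol's own 0.05. What the defence does not rescue is the power figure. Section 12.3 attaches 90% to an explicit integer rule without calling it approximate, and a gap of 9.6 points is not rounding.

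A second objection concerns the consequence. A reader might infer that a programme at 80% adherence is rejected one time in five. Section 12.3 does not say so. It says that 15 or more would warrant further investigation and gives 50% or fewer as grounds to reject; it assigns no action to 11 to 14 of 20. If the 50% limit is read as an observed rate, P(X ≤ 10 | 20, 0.80) is only 0.003. The supportable statement is that such a programme misses the 15-of-20 criterion 19.6% of the time.

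Third, the error is conservative against a false go: exact α is 0.021 against 0.05. That is true, and it is why the rule itself can stand.

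**Conclusion.** The stated power is wrong for the stated rule. At 80% adherence, at least 15 of 20 has exact power of 80.4%, not 90%; the chance of missing the criterion is 19.6%, not the implied 10%; and the exact one-sided type I error is 0.021. This assumes 20 analysable patients whose adherence outcomes are independent with a common probability. It does not depend on sidedness or on which version of the sample-size formula was used.

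The sample size and cut-off are not miscalculated from the named method, and the go criterion is not invalid. The defect is that nominal large-sample power is presented as the power of an integer rule. It needs correcting because the figure describes the primary decision criterion.

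**What to change.** Keep 20 analysable patients and the cut-off of 15. In Section 12.3, and in any SAP that repeats it, replace the power statement with: at least 15 of 20 adherent gives exact one-sided alpha 0.021 and power 80% at a true adherence of 80%.

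The cost is one sentence and a less favourable stated power. Recruitment, conduct and the primary analysis do not change.

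Two other repairs look tempting and are not advised.

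- **Lowering the cut-off to 14.** This breaks the protocol's p=0.05 (exact α 0.058). It would also loosen the success criterion in an open trial that, by the account of the allocation change in Section 12.3, is already under way.
- **Relying on more analysable patients to recover 90%.** The smallest exact design with α ≤ 0.05 and power ≥ 90% is at least 16 of 23 (α 0.047, power 92.8%). With 26 recruited and the protocol's 25% dropout, the expected number analysable is 26 × 0.75 = 19.5. Treating dropout as binomial, the chance of 23 or more is about 0.08.

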## 2.1 Lay summary

People with lung cancer receive chemotherapy to improve symptoms and survival. However, chemotherapy can make leg muscles weak. The reason is unclear, but may relate to reduced activity due to fatigue. Maintaining leg muscle strength is important as this helps determine how active and independent a person is.

Exercise helps maintain leg muscle strength, but even simple forms, e.g. walking, can be difficult when fatigued. An alternative form of exercise is the use of neuromuscular electrical stimulation (NMES). A small battery operated stimulator with two pads placed over each thigh produces a controlled, comfortable, slow contraction and relaxation of the underlying muscles while the person is seated. Our group recently found that NMES 30min daily for one month improved leg muscle strength and physical activity levels in people with lung cancer not on chemotherapy.

NMES looks a promising therapy. However, to determine if NMES is worth pursuing, we wish to examine if it is acceptable to a larger group of people. Given that chemotherapy weakens leg muscles, it is also appropriate that we examine its use in this setting. We would also like to explore further why chemotherapy causes leg muscle weakness.

47 people due to receive chemotherapy will be required for the study. One third will be randomised to receive usual care and two thirds to receive usual care plus NMES. The NMES group will be asked to use the treatment on both legs daily throughout their 3–4 cycles of chemotherapy. Acceptability of NMES will be assessed by diary records of how much the stimulator is used. The potential benefit of NMES will be explored by assessing leg muscle strength, muscle size and physical activity levels, and asking people about their experiences. We will also explore why leg muscles become weaker during chemotherapy by assessing fatigue and nutritional factors and documenting the response of the cancer to chemotherapy. The intervention will be monitored for safety in real time.

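### Section 12.3's claim that the switch from 1:1 to 2:1 leaves integrity unaffected holds for the primary endpoint but not for the between-arm strength comparison, which should adjust for allocation phase

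*Protocol*

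**What the plan says.** Section 12.3 of the protocol records the history of the allocation ratio: "Originally the trial started by randomising with a 1:1 allocation", and later "this was changed to a 2:1 in favour of the NMES arm allocation part way through the trial in order to support recruitment". It then concludes: "As the study analysis is based on a within-intervention arm analysis, the statistical integrity of the study is not affected". The same section says that the control arm is there so that some secondary endpoints can be compared, and gives the resulting target as "47 patients would need to be recruited in total (26 to the treatment arm and 21 to the control arm").

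Section 12.5 plans such a comparison. By intention to treat, "change in leg muscle strength from baseline will be compared between trial arms" at 9, 17 and 20 weeks. It names no test, model or covariates, and refers to a full statistical analysis plan to be written before the first interim analysis. Strength is the only outcome for which that section plans a comparison between arms. QoL, body composition, nutritional intake and fatigue are to be presented descriptively, and response is described by arm. Secondary objectives ii and iii in Section 3.0 ask whether NMES can influence the changes seen during and after chemotherapy.

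On the ratio itself, the lay summary in Section 2.1 says of the 47 participants: "One third will be randomised to receive usual care and two thirds to receive usual care plus NMES". Section 4.0 likewise describes 47 patients randomised 2:1. Neither mentions the 1:1 period.

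**The concern.** The reason given in Section 12.3 covers less than the conclusion drawn from it. An analysis confined to one arm is indeed indifferent to the allocation ratio. A comparison between arms is not, once the ratio changes part way: patients recruited later are then over-represented in the NMES arm relative to control. If strength change differs between early and late recruits for any reason unrelated to NMES (case mix, chemotherapy practice and assessor experience are the usual candidates), a comparison that pools the two periods attributes part of that difference to NMES.

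At stake is the estimate of the NMES effect on strength. Section 3.0 says the trial should help determine whether a phase III trial is feasible and justified, and this estimate will be read for that purpose. As worded, the sentence also suggests to whoever writes the analysis that the switch can be ignored. The flat 2:1 in Sections 2.1 and 4.0 hides the switch and misstates the expected size of the control arm.

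**Working it through.** **Inputs.** From Section 12.3: 20 evaluable NMES patients, about 25% dropout, 26 NMES and 21 control patients, 1:1 at first and then 2:1. Not in the documents, so assumed: exact balance within each phase, the size of any drift D between phases (in SDs of strength change), and the baseline to follow-up correlation r.

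**1. The plan's own target.** 20/0.75 = 26.7, against the stated 26 (rounding up would give 27, a trivial difference). 26 + 21 = 47, as stated.

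**2. Implied phases.** Let a be the number per arm under 1:1 and b the number of controls under 2:1.

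- NMES: a + 2b = 26
- Control: a + b = 21
- Hence b = 5 and a = 16: 16:16 in the first phase, 10:5 in the second, and 32 + 15 = 47.

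The protocol does not state how many had been randomised at the switch, so this split is an inference.

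**3. Association of arm with period.** Second-phase patients make up 10/26 = 38.5% of the NMES arm and 5/21 = 23.8% of controls. The gap is 0.385 - 0.238 = 0.147. The bias of a pooled difference in means is therefore 0.147 x D. If later recruits fare worse, NMES looks worse than it is; if they fare better, it looks better.

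The factor depends on exact balance. With one patient fewer in the first phase it would be 15/21 - 16/26 = 0.10 (16:15 then 10:6) or 16/21 - 15/26 = 0.18 (15:16 then 11:5).

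**4. Size against the standard error.** In SD units the standard error is sqrt(1/26 + 1/21) = 0.293 with all patients. With 20 and 16 patients (25% dropout taken to apply to both arms) it is sqrt(1/20 + 1/16) = 0.335.

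| Assumed drift D (SD) | Bias (SD) | Bias/SE, 26 v 21 | Bias/SE, 20 v 16 |
|---|---|---|---|
| 0.25 | 0.037 | 0.13 | 0.11 |
| 0.5 | 0.073 | 0.25 | 0.22 |
| 1.0 | 0.147 | 0.50 | 0.44 |

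**5. Type I error.** In 20,000 simulated trials per setting with 26 and 21 patients, the two-sided 5% t-test that ignores phase rejected in 5.0% at D = 0.5 and 5.3% at D = 1. The drift shifts the estimate but also widens the observed SD. A normal approximation that holds the SD fixed gives 5.7% and 7.9%. The model with a phase term had simulated bias of essentially zero.

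**6. Cost of adjusting for phase.** The variance within the first phase is 1/16 + 1/16 = 0.125 and within the second 1/10 + 1/5 = 0.300. Combined, this gives 1/(1/0.125 + 1/0.300) = 0.0882, against 0.0861 for the pooled comparison without drift. The ratio is 1.025, so 2.5% more variance.

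**7. Baseline strength, a separate matter.** With equal variances at both times, an unadjusted change score has variance proportional to 2(1 - r), and a baseline-adjusted analysis 1 - r². The ratio is (1 + r)/2: 0.75, 0.85 and 0.90 for assumed r of 0.5, 0.7 and 0.8. This gain does not depend on the allocation switch.

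**8. Flat 2:1 against the target.** 47 at 2:1 would be about 31:16. Section 12.3 has 26:21, or 55%:45%.

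**The case against.** The strongest reply is that the sentence sits in the sample size section, which opens by saying the trial is powered on the intervention arm alone. Read there, it may be meant only for the primary endpoint, and for that endpoint it is correct. This explains the wording but does not rescue it: the sentence speaks of the statistical integrity of the study, in a paragraph that has just given the control arm a comparative role. A SAP could handle the switch properly, but it could not make the reason given cover the comparison in Section 12.5.

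A second reply is that the bias is small and conditional. That stands. No drift is documented, the trial runs at one centre, and the comparison is an unpowered secondary one in a phase II feasibility trial. Without drift there is no bias.

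A reader might infer that Section 12.5 prescribes a crude, unadjusted comparison. It does not. It names change from baseline as the outcome and leaves the model open, and a model of change on arm and baseline strength would satisfy its wording.

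A reader might also infer that the stratification factors have been left out of the analysis. Section 12.1 says of the blocked randomisation: "This will ensure balanced treatment allocation by a number of clinically important stratification factors". It names none of the factors and does not mention allocation phase, but whether they enter the model is ordinary SAP content, and silence here is not a decision.

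Finally, Sections 7.0 and 12.1 give the ratio now in operation and need not recount its history. That is fair. It does not excuse Sections 2.1 and 4.0, which describe the whole trial of 47.

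**Conclusion.** The point holds in a limited form. The integrity statement is true for the primary adherence proportion and too broad for the planned between-arm comparison of strength change. Under the inferred split, a comparison that ignores allocation phase carries 0.147 of any between-phase shift: 0.04 to 0.15 SD for assumed drifts of 0.25 to 1 SD, or about 0.1 to 0.5 standard errors. This is a modest, avoidable bias in a secondary estimate.

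The documents do not support reading this as a compromised trial or a seriously inflated error rate. The primary decision rule does not use the control arm, and simulated type I error of the pooled test stays near 5% even at a 1 SD drift. Baseline adjustment is worth having for precision but does not follow from the switch. The result rests on exact balance within each phase and on drift values that the protocol does not supply. The inconsistency between 2:1 for all 47 and 26:21 rests on no assumption.

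**What to change.** - **Section 12.3:** limit the integrity sentence to the primary adherence endpoint.
- **Section 12.5:** state that the between-arm strength comparison adjusts for allocation phase (1:1 or 2:1) and for baseline strength. Change from baseline can remain the outcome, since with baseline in the model the arm effect is the same as for follow-up strength. Use of the stratification factors can be left to the SAP.
- **Sections 2.1 and 4.0:** say that allocation was 1:1 at first and then 2:1, with a target of 26:21 in total.

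The cost is wording and one model term each for phase and baseline. Phase follows from the date of randomisation, and baseline strength is already collected under Section 9.1. If there is no drift, the phase term costs about 2.5% in variance. Against an unadjusted change score, the baseline term returns more than that at each of the correlations considered above.
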